### Statistical analysis plan

#### Sample size estimation

The sample size of participants was estimated based on the prevalence of adverse outcomes among CU patients, including (i) inadequate response to a standard dose of H1-antihistamines or uncontrolled urticaria symptoms (UCT score <12) with a range of 28.7%–82.8% [3, 8, 12, 13]; (ii) HRQOL impairment (DLQI >10 points) with a range of 30.9%– 31.5% [7, 8]; and (iii) mental health and psychosocial problems (depression, anxiety, insomnia, and somatic symptoms) with a range of 17.2%–55.7% [6, 7, 9]. With respect to a design effect of 2.0 and missing data of 20%, a target of at least 132 CU patients will be required for this study to ensure a 10% of margin of error and 0.05 type I error. Nevertheless, there will be no restrictions on the number of participants in this prospective longitudinal study.

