#### Statistical analysis

Preplanned statistical analysis will be performed based on one-year follow-up care (Table 3). The characteristics of the study cohort will be described as frequencies with percentages for categorical variables and mean ± standard deviation or medians with interquartile range for continuous variables as suitable. The differences between treatment groups (treatment-based non-sedating second-generation H1-antihistamines, biologics, or immunosuppressive agents) or severity strata of urticaria symptoms based on UAS7 (mild, 7–15 points; moderate, 16–27 points; and severe, 28–42 points) for categorical and continuous variables will be compared using Fisher’s exact test and analysis of covariance or Kruskal-Wallis test, respectively.

The point prevalence of adverse health outcomes (e.g., treatment responses [response vs. refractory to first-line therapy with non-sedating second-generation H1-antihistamines], symptoms controlled [uncontrolled, UCT <12 points vs. controlled, UCT ≥12 points], and occurrence of adverse mental health issues [including HRQOL impairment, depression, anxiety, insomnia, and somatic symptoms) will be estimated and reported corresponding to 95% confidence intervals (95% CIs). Subgroup analyses will be performed based on key patient characteristics (i.e., age of study participants, female sex, duration of CU, severity of urticaria symptoms, subtypes of CU, body weight/body mass index, total immunoglobulin E level, history of allergy or other systemic diseases, specific pharmacological treatments, and concomitant and rescue medications). In addition, one-year follow-up findings will be compared to assess the long-term response to the prevalence of adverse health outcomes. The overall trend analysis will explore the effect of over time across the cohort time frame.

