For cross-sectional analyses, the crude association among participant characteristics will be explored using the univariable logistic regression models to identify the candidate risk factors for adverse health outcomes. Subsequently, candidate risk factors with a *P*-value of <0.100 will be included in the multivariable logistic regression analysis with the backward elimination method. The variance inflation factors of risk factors within the multivariable model will be investigated to detect the multicollinearity of the final model. The odds ratios (ORs) with 95% CIs will be reported as the effect estimates of the final set of risk factor models for adverse health outcomes. For longitudinal analyses, changes in the adverse health outcome status during the follow-up period will be analyzed using multilevel logistic regression models with random intercepts to explore the associations with individual-level and baseline predictors.

All analyses will be performed using Stata software (version 16.0; StataCorp LP). Statistical significance for all tests will be two-tailed, with a *P*-value of <0.05. For participants with missing covariates, multiple imputation methods will be used to analyze incomplete datasets. However, variables containing more than 20% of missing data will be excluded from all analyses.

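### The target of 132 fits only a prevalence of 17.2% or 82.8%, so on the plan's own inputs the 10% margin of error is missed for most of the outcomes it is claimed for

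*Protocol article*

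**What the plan says.** The section on sample size estimation in the protocol article bases the calculation on the prevalence of three groups of adverse outcomes:

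- inadequate response to antihistamines or uncontrolled symptoms, 28.7–82.8%;
- "HRQOL impairment (DLQI >10 points) with a range of" 30.9–31.5%;
- mental health and psychosocial problems, 17.2–55.7%.

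It applies a design effect of 2.0 and 20% missing data and concludes that "a target of at least 132 CU patients will be required for this study to ensure a 10% of margin of error", at a type I error of 0.05. It does not say which prevalence was entered. It adds that recruitment has no upper limit.

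The section on statistical analysis plans point prevalences of these outcomes with 95% confidence intervals. It also states: "Statistical significance for all tests will be two-tailed, with a *P*-value of <0.05". The abstract likewise presents prevalence with a 95% interval as a planned result.

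**The concern.** The statement is a guarantee of precision for three outcome families together, but one target can give that guarantee only if it is sized for the prevalence that needs the most patients. For a fixed absolute margin that is 50%, which lies inside two of the three quoted ranges. A target of 132 looked low for a design effect of 2.0 and 20% missing data at mid-range prevalences.

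This calculation is the only justification given for the cohort size. Health-related quality of life is named in the primary objectives, and its quoted range is narrow and well away from the extremes. A reader who relies on the stated margin would expect intervals of ±10 points for that outcome, and the plan's own assumptions do not give them.

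**Working it through.** **Inputs**

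From the sample size section: absolute margin d = 0.10; type I error 0.05; design effect (DEFF) 2.0; missing data 20%; the prevalence endpoints above. From the statistical analysis section: two-sided testing and 95% intervals, hence z = 1.96. I added 50% because it lies inside the first and third ranges and is the hardest case.

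**Reproducing 132**

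n0 = z² p(1−p) / d². At p = 0.172 or 0.828:

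1.96² × 0.172 × 0.828 / 0.01 = 54.71

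54.71 × 2.0 × 1.2 = 131.3, rounded up to 132.

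The section prints no formula, so the factor of 1.2 for missing data is inferred from this exact match. Dividing by 0.8 instead gives 54.71 × 2.0 / 0.8 = 136.8, so 137. I tried every quoted endpoint and 50%, with DEFF 1 or 2 and with the missing-data allowance as ×1.2, as ÷0.8 or omitted. Only 17.2% and 82.8% with DEFF 2.0 and ×1.2 return 132.

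**Required size at the other prevalences (DEFF 2.0)**

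| Prevalence | n0 | N, ×1.2 | N, ÷0.8 |
|---|---|---|---|
| 17.2% or 82.8% | 54.71 | 132 | 137 |
| 28.7% | 78.61 | 189 | 197 |
| 30.9% | 82.03 | 197 | 206 |
| 31.5% | 82.89 | 199 | 208 |
| 55.7% | 94.79 | 228 | 237 |
| 50% | 96.04 | 231 | 241 |

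**Half-width with 132 enrolled**

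Half-width = 1.96 × √(p(1−p) / n_eff). With 20% missing, 132 × 0.8 = 105.6 are analysed, so n_eff = 105.6 / 2 = 52.8. Undoing the ×1.2 inflation instead gives n_eff = 132 / 2.4 = 55. The last column drops the design effect and keeps the 20% loss (n_eff = 105.6).

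| Prevalence | n_eff 52.8 | n_eff 55 | No DEFF, 105.6 |
|---|---|---|---|
| 17.2% or 82.8% | 10.2 | 10.0 | 7.2 |
| 28.7% | 12.2 | 12.0 | 8.6 |
| 30.9% | 12.5 | 12.2 | 8.8 |
| 31.5% | 12.5 | 12.3 | 8.9 |
| 55.7% | 13.4 | 13.1 | 9.5 |
| 50% | 13.5 | 13.2 | 9.5 |

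(percentage points)

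**Where the 10-point margin holds**

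With n_eff = 55 it holds only for prevalences up to 17.3% or from 82.7% upwards. With n_eff = 52.8 the limits are 16.5% and 83.5%, so no quoted value meets it. Even with all 132 analysed and DEFF 2.0 (n_eff = 66), the half-width is 11.2 points at 31.5% and 12.1 at 50%.

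**The case against.** The strongest objection is that the shortfall comes entirely from the design effect of 2.0, and nothing in the described sampling produces one. Individual adults are recruited consecutively at one clinic, and a point prevalence uses one observation per patient. The analysis section does not say that the reported intervals will be widened by a design effect. Without it, 132 patients with 20% missing give at most 1.96 × √(0.25 / 105.6) = 0.095, so the 10-point margin would hold for every outcome. This stands as a limit on the practical consequence: the reported intervals may well be narrower than 12.5 points. It does not rescue the sentence, which states the design effect and claims the margin with it included.

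Other points:

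- The target is a minimum and there is no cap. That is so, but the text says 132 is what secures the margin. The cohort status section reports 75 participants as of August 10, 2022, so a larger cohort cannot be presumed.
- A z of 1.645 at 28.7% gives 133, close to the target. It conflicts with the two-tailed 0.05 level and the 95% intervals in the analysis section. It would still leave quality of life needing 139–141 patients and 50% needing 163.
- The ×1.2 factor is inferred, and the half-widths depend on the missing-data convention. The two conventions differ by only 0.2 to 0.3 points.
- This is an observational cohort, no decision is tied to the margin, and the achieved intervals will be visible in the report. That makes the effect moderate; the statement remains incorrect.

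**Conclusion.** The concern holds. On the plan's stated inputs (two-sided 95%, design effect 2.0, 20% missing data), 132 is the requirement for the quoted prevalences that need the fewest patients. The claimed 10-point margin is missed at every quoted value for impaired quality of life (about 12.5 points) and over nearly all of the other two ranges (up to 13.5 points). Meeting the claim at every prevalence would take 231 patients on the plan's apparent arithmetic, 75% more than 132 (231 / 132 = 1.75).

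The conclusion takes the design effect as the plan states it. Whether that factor belongs in the formula is a separate question; if it is withdrawn, the margin is at most 9.5 points and the 10-point claim becomes true. As printed, the inputs, the target and the margin do not agree.

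**What to change.** Keep 132, state the planning prevalence that was used, and replace the precision claim with wording such as:

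> With a design effect of 2.0 and 20% missing data, 132 patients give a 95% margin of error of about 10 to 13.5 percentage points across the prevalences considered (about 12.5 for impaired quality of life).

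If the sponsor decides that the design effect does not apply and removes it, the sentence should say instead that 132 patients with 20% missing data give a margin of at most 9.5 percentage points at any prevalence.

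The cost is one sentence in the sample size section. No extra patients and no change of design are needed. With the design effect kept, the stated precision becomes less favourable.

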#### Statistical analysis

Preplanned statistical analysis will be performed based on one-year follow-up care (Table 3). The characteristics of the study cohort will be described as frequencies with percentages for categorical variables and mean ± standard deviation or medians with interquartile range for continuous variables as suitable. The differences between treatment groups (treatment-based non-sedating second-generation H1-antihistamines, biologics, or immunosuppressive agents) or severity strata of urticaria symptoms based on UAS7 (mild, 7–15 points; moderate, 16–27 points; and severe, 28–42 points) for categorical and continuous variables will be compared using Fisher’s exact test and analysis of covariance or Kruskal-Wallis test, respectively.

The point prevalence of adverse health outcomes (e.g., treatment responses [response vs. refractory to first-line therapy with non-sedating second-generation H1-antihistamines], symptoms controlled [uncontrolled, UCT <12 points vs. controlled, UCT ≥12 points], and occurrence of adverse mental health issues [including HRQOL impairment, depression, anxiety, insomnia, and somatic symptoms) will be estimated and reported corresponding to 95% confidence intervals (95% CIs). Subgroup analyses will be performed based on key patient characteristics (i.e., age of study participants, female sex, duration of CU, severity of urticaria symptoms, subtypes of CU, body weight/body mass index, total immunoglobulin E level, history of allergy or other systemic diseases, specific pharmacological treatments, and concomitant and rescue medications). In addition, one-year follow-up findings will be compared to assess the long-term response to the prevalence of adverse health outcomes. The overall trend analysis will explore the effect of over time across the cohort time frame.

For cross-sectional analyses, the crude association among participant characteristics will be explored using the univariable logistic regression models to identify the candidate risk factors for adverse health outcomes. Subsequently, candidate risk factors with a *P*-value of <0.100 will be included in the multivariable logistic regression analysis with the backward elimination method. The variance inflation factors of risk factors within the multivariable model will be investigated to detect the multicollinearity of the final model. The odds ratios (ORs) with 95% CIs will be reported as the effect estimates of the final set of risk factor models for adverse health outcomes. For longitudinal analyses, changes in the adverse health outcome status during the follow-up period will be analyzed using multilevel logistic regression models with random intercepts to explore the associations with individual-level and baseline predictors.

All analyses will be performed using Stata software (version 16.0; StataCorp LP). Statistical significance for all tests will be two-tailed, with a *P*-value of <0.05. For participants with missing covariates, multiple imputation methods will be used to analyze incomplete datasets. However, variables containing more than 20% of missing data will be excluded from all analyses.

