## Introduction

Chronic urticaria (CU) is a chronic inflammatory skin disease characterized by the presence of recurrent hives (wheals), and/or angioedema for longer than six weeks [1]. According to global epidemiology estimates, CU is a common disease that affects adults, with a point prevalence of 0.86% [2]. However, it has been revealed to increase over time, in particular, up to 1.5% in Latin America and 1.4% in Asian countries [2]. CU is recognized as chronic spontaneous urticaria (CSU, lesions occur spontaneously), chronic inducible urticaria (CIndU, lesions occur in response to explicit triggers), or both (co-existence of CSU and CIndU). With respect to the subtypes of CU, approximately two-thirds of patients with CU were characterized as CSU [3], and 20.2% of patients were diagnosed as having a combination of CSU and CIndU [4].

On the basis of patient and society’s perspective, individuals living with CU are significantly negatively affected by a wide spectrum of disease burdens, including high impact on health-related quality of life (HRQOL), impaired school/work performance, limited activity and physical function, worsened mental health and well-being issues, psychosocial problems (i.e., impaired family life, partnerships, and social interactions), and high costs and economic burden [5–9]. Moreover, existing studies have revealed that CU patients place a significant burden of illness higher than other chronic skin diseases [9, 10].

Although the current European Academy of Allergology and Clinical Immunology (EAACI)/Global Asthma and Allergy European Network (GA^2^LEN)/European Dermatology Forum (EDF; EuroGuiDerm)/Asia Pacific Association of Allergy, Asthma and Clinical Immunology (APAAACI) international guidelines suggest effective licensed doses of non-sedating second-generation H1-antihistamines as the first-line therapy for the management of CU and there is substantial evidence of its effectiveness [1, 11], CU patients are often inadequately controlled for urticaria symptoms with this first-line therapy [3, 8, 12, 13].

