### Study population

Adult patients in an outpatient urticaria clinic will be consecutively recruited for this research. The study population will consist of adult patients diagnosed with CU (duration >6 weeks) based on the EAACI/GA^2^LEN/EuroGuiDerm/APAAACI Guideline on urticaria [1]. Both CSU and CIndU are included (Table 1). The inclusion and exclusion criteria for the longitudinal cohort are shown in Table 2.

**Table 1 pone.0279566.t001:** Classification of chronic urticaria subtypes [1].

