### Pre-specified outcomes of interest

The pre-specified outcomes of interest and assessment of the CORE-CU cohort included the following (Table 3):

Clinical outcomes
Urticaria symptoms and severity using the daily urticaria activity score (daily UAS) and urticaria activity score over 7 days (UAS7) [1]Urticaria symptom control using the Short Form Urticaria Control Test (UCT) [14], Patient’s Global Assessment of Disease Control-Likert Scale (PatGA-LS) [15], and Patient’s Global Assessment of Disease Severity-Visual Analog Scale (PatGA-VAS) [15]Safety profiles: occurrence of adverse eventsPRO measures
HRQOL using the Chronic Urticaria Quality of Life Questionnaire (CU-Q2oL) [16], Dermatology Life Quality Index (DLQI) [17], and EuroQoL-5 dimension-5 level (EQ-5D-5L)Mental health issues and psychosocial problems using the Patient Health Questionnaire 9-item (PHQ-9) [18], Generalized Anxiety Disorder 7-item (GAD-7) [19], and the 5-item World Health Organization Well-being Index (WHO-5) [20]Symptom burden and impact on sleep using the Somatic Symptom Scale 8-item (SSS-8) [21] and Insomnia Severity Index (ISI) [22]Medication adherence using the Medication Adherence Scale in Thais (MAST) [23]Satisfaction with care using the global visual analog scale-10 cm and our team development version toolWork impairment using the Work Productivity and Activity Impairment Instrument (WPAI) [24]Health care utilization and economic outcomes
Health care costs: direct medical costs, direct non-medical costs, and indirect costsHospitalization, emergency visits, and extra/unplanned visits during the follow-up

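### UAS7 severity strata cover the whole cohort, but in purely inducible urticaria a 7-day symptom sum is confounded by how often the trigger was met

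*Protocol article*

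**What the plan says.** All references are to the protocol article.

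- **Population.** The Study population section states "Both CSU and CIndU are included (Table 1". Table 1 lists nine inducible forms, and eligibility (Table 2) does not exclude any of them.
- **Definition.** The Introduction describes "chronic inducible urticaria (CIndU, lesions occur in response to explicit triggers". It also recognises patients who have both forms.
- **Expected mix.** The Introduction cites literature in which "approximately two-thirds of patients with CU were characterized as CSU", and adds that "20.2% of patients were diagnosed as having a combination of CSU and CIndU".
- **Instrument.** Under Pre-specified outcomes of interest, the first clinical outcome is "Urticaria symptoms and severity using the daily urticaria activity score (daily UAS) and urticaria activity score over 7 days (UAS7", with no condition on subtype. Table 3 schedules the UAS monthly for everyone.
- **Analysis.** The Statistical analysis section compares variables between treatment groups or "severity strata of urticaria symptoms based on UAS7", with cut-offs of 7–15 for mild, 16–27 for moderate and 28–42 for severe. The subgroup list there names "severity of urticaria symptoms, subtypes of CU" as separate factors.
- **Other measures.** The UCT, PatGA-LS and PatGA-VAS are also monthly in all participants (Table 3). Symptom control is analysed by the UCT at a cut-off of 12. The severity strata use none of these three.

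**The concern.** A 7-day sum adds up daily symptom scores. In spontaneous disease that total is a natural reading of how active the disease is. In purely inducible disease, by the protocol's own definition, symptoms need a trigger, so the total mixes how strongly the patient reacts with how many days the trigger was met. Someone who avoids the trigger successfully can score low with a strong underlying reaction.

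The plan makes this score a grouping variable. Patients of different subtypes are placed in the same strata, and patient-reported outcomes, costs and other variables are then compared between strata. A purely inducible patient may sit in a low stratum, or in none, because exposure was low that week. The possible misplacement goes with subtype, so a contrast between strata carries subtype and exposure along with severity. The severity subgroup analysis has the same weakness.

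**Working it through.** **1. Range of scores for one and the same disease**

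Input: the top of the severe band is 42 points over 7 days (Statistical analysis). Daily maximum = 42 / 7 = 6.

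Illustrative assumption: the patient has the worst possible day on each day of exposure and no symptoms on the other days. Then UAS7 = 6 × number of exposure days.

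| Exposure days | UAS7 | Listed stratum |
|---|---|---|
| 0 | 0 | none (below 7) |
| 1 | 6 | none (below 7) |
| 2 | 12 | mild (7–15) |
| 3 | 18 | moderate (16–27) |
| 4 | 24 | moderate |
| 5 | 30 | severe (28–42) |
| 7 | 42 | severe |

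The reaction to the trigger is identical in every row, and only the number of exposure days changes. This is a bounding example, not an estimate of how many patients are misplaced.

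**2. How many patients could be affected**

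Inputs: about 2/3 of CU is CSU and 20.2% have both forms (Introduction); the target is 132 (Sample size estimation); 75 were enrolled on August 10, 2022 (Cohort status).

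The target is used here only as a denominator. It reproduces at a prevalence of 17.2% (or 82.8%) with a 10% margin of error: 1.96² × 0.172 × 0.828 / 0.10² = 54.7. Then 54.7 × 2.0 = 109.4, and 109.4 × 1.20 = 131.3, rounded up to 132.

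The article does not say whether the mixed group is counted within the two-thirds.

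- Mixed group inside the two-thirds: purely inducible = 1 − 2/3 = 33.3%. That is 132 × 0.333 = 44 patients, or 75 × 0.333 = 25 of those enrolled.
- Mixed group outside the two-thirds: purely inducible = 33.3% − 20.2% = 13.1%. That is 132 × 0.131 ≈ 17 patients, or about 10 of those enrolled.

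**3. Does the planned subtype subgroup repair it?**

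Subtype and severity stand as separate factors. An analysis by subtype leaves the strata as they are, and the comparison across strata still pools subtypes. Within the inducible subgroup, the strata remain dependent on exposure.

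**The case against.** The strongest reply is that the score does what its label says. The article speaks of severity of urticaria symptoms, and a patient who met no trigger did have few symptoms that week. This stands in part: UAS7 still reflects symptoms experienced, so the defect is confounding by exposure and not a score that ignores severity.

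Second, much of what is needed is already in the plan: UCT-based control, monthly PatGA measures, a subtype subgroup and a one-year comparison. This stands too, and it confines the problem to analyses that group by or summarise UAS7. It does not repair those.

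Third, the UCT and PatGA are also patient-reported and may fall when a trigger is avoided. Nothing in the article shows them to be free of exposure, so they are a better-separated report for inducible patients and not a clean severity scale.

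Three stronger readings are tempting, and the article does not support them:

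- *A reader might infer that UAS7 would track season.* The article never mentions season. The idea is plausible only for some Table 1 forms, such as cold, heat, solar or cholinergic urticaria, and no share is given for these.
- *A reader might infer that UAS7 change at months 3 to 9 would be taken as treatment response.* No section defines response by UAS7 or plans a UAS7 change analysis. The longitudinal models use adverse health outcome status, and control is defined by the UCT.
- *A reader might infer that trigger exposure is never recorded.* Table 3 is a condensed schedule that includes medical history at each quarterly visit, and the case record form is not shown. Silence in the article does not settle this.

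**Conclusion.** The point holds in a limited form. Comparing outcomes across UAS7 strata in the whole cohort, and using severity as a subgroup factor, confounds severity with trigger exposure in purely inducible patients. The conclusion rests on the protocol's own definition of CIndU and its own cut-offs, and needs no outside evidence on the instrument.

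The group concerned is about 13% to 33% of patients, or about 17 to 44 of 132. These are literature shares quoted in the article, and one third is the top of the range. The size and direction of any bias in the stratum comparisons cannot be derived from the article. The UCT-based prevalence of uncontrolled symptoms does not use these strata and is outside this point. The change is worth making before analysis, but it does not undermine the study as a whole.

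**What to change.** In the analysis plan:

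1. Restrict the UAS7 severity strata, the severity subgroup analysis and any UAS7-based summary of change to patients with a spontaneous component, that is CSU alone or CSU with CIndU.
2. Report purely inducible patients separately, using the UCT, PatGA-VAS and PatGA-LS.
3. State that these measures may also partly reflect exposure to the trigger.
4. Report the number of patients with CSU alone, CIndU alone and both, so that the size of the restriction is visible.

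This changes wording only. Subtype is already part of the medical history data and the three alternative measures are already collected monthly. The cost is a smaller denominator for the UAS7 analyses: at the target of 132, about 88 (132 − 44) to 115 (132 − 17) patients would remain under the shares above.
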